## Procedures

### Eligibility screening

Participants of the CCSS cohort who received radiation for their childhood cancer and were not known to have a personal history of skin cancer are eligible to participate. Recruitment for the current intervention coincided with the release of the CCSS Follow-Up 5 (FU5) survey; therefore, FU5 is utilized as a recruitment screening tool. Individuals who fulfill the criteria listed above are sent the screening questions: (1) Have you been diagnosed with a skin cancer; (2) Have you seen a regular health care provider in the past 2 years, or do you plan to see one in the next year; (3) Do you have a mobile phone that can receive text messages; and, (4) Do you have access to a smartphone or tablet? Participants are eligible to participate in the ASK study if they answer ‘no’ to the first question and ‘yes’ to the remaining questions.

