### Study participants

The study will be conducted using the cohort of the Childhood Cancer Survivor Study (CCSS), funded by NCI grant U24 CA55727 (Principal Investigator, [name]). This cohort includes participants from 50 states diagnosed with a childhood cancer between 1970 and 1986 before age 21 years. Participants have been recruited by 27 clinical sites in the United States (US) and Canada. As of 2007, there were 12,323 known living participants, 46% of the sample were female, median age was 36 years, 73% were under age 40 years, 88% were White, non-Hispanic, and 25% had at least a college education [33-35].

Eligibility criteria for the ASK study include: (1) current age of 18 years or older; (2) previously treated with radiation for childhood cancer; (3) having seen their primary care physician or oncologist in the previous 2 years or planning to do so in the next year; (4) having no personal history of a skin cancer diagnosis, (5) possession of a cellular phone that can receive text messages, and (6) access to a DermLite (3Gen, San Juan Capistrano, CA, USA) compatible smartphone or tablet. Informed consent will be obtained from each enrolled participant in the ASK study.

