### Recruitment

The study protocol was reviewed and approved by the Institutional Review Board of Harvard TH Chan School of Public Health (approval number: IRB12-0002). Participants who meet study eligibility criteria will be invited to enroll. The invitation packet includes the invitation letter, Health Insurance Portability and Accountability Act (HIPAA) authorization, consent form, and the baseline survey.

Upon receipt of the completed survey and HIPAA authorization, the participant is officially enrolled in the study and randomized to one of three study arms. Within 7 days of randomization, each participant receives an enrollment packet that includes: a letter welcoming them to the study; print materials about their skin cancer risk, how to conduct skin self-examinations, an appointment checklist providing tips and suggestions about physician skin examinations for participants to reference when they go to see their doctor; and details about how to access the study website. Participants in Arm 3 also receive the dermatoscope and instructions for attaching it to their smartphone, using it, and uploading photos to the photo repository.

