#### Arm 3: Patient Activation and Education plus physician activation and teledermoscopy

In addition to PAE + MD, Arm 3 participants receive a dermatoscope that permits acquisition of dermoscopic images through the participant’s smartphone camera and instructional materials for use of this attachment including a customized instructional video. Participants can take high-resolution photographs of suspect moles or lesions and upload these photos via a secure web portal for review by the study dermatologist. Participants are instructed to ask significant others to take photographs of back-of-body lesions. A letter with the results of the assessment of submitted photographs to the study website will be sent to the participant’s identified physician encouraging the physicians to emphasize the importance of monthly self-examinations and encouraging referral to a dermatologist for a clinical examination, if necessary. Participants are informed that they must contact their physicians to receive dermoscopy reports. Participants have access to teledermoscopy for 12 months after enrollment.

The study staff, in cooperation with 3Gen, the manufacturer of the DermLite, developed written and video instructional materials to assist participants in effectively using the DermLite attachment and ensuring proper upload of photographs taken to be reviewed by the study dermatologist. The DermLite (Figure 2) is a portable dermatoscope that can be attached to smartphones and tablets and is primarily used for the examination of suspicious skin lesions. It consists of a magnification lens and light-emitting diode (LED) lighting that allows high-quality visualization of subsurface skin structures that are not typically visible to the naked eye. Advantages of this technology are that it can facilitate detection of skin cancers in the early stages of development and offers the possibility of increased convenience for both physicians and patients as it has the potential to be performed by the patient and sent remotely to a physician specialist. Print and online materials provided for Arm 3 participants include step-by-step instructions regarding the use of the DermLite, troubleshooting tips, and detailed instructions about uploading photos via the study website.

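### The screening question does not check the DermLite-compatibility criterion, so participants who may be unable to use teledermoscopy can be randomized to Arm 3

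*Protocol article*

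**What the plan says.** The two places that define who may enter the trial differ on the device.

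- **Study participants**, criterion 6: "access to a DermLite (3Gen, San Juan Capistrano, CA, USA) compatible smartphone or tablet".
- **Eligibility screening**, question 4: "Do you have access to a smartphone or tablet". Compatibility is not mentioned. The section closes with the operative rule: "Participants are eligible to participate in the ASK study if they answer" no to the skin cancer question and yes to the other three.

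The questions go to a preselected group: "Individuals who fulfill the criteria listed above are sent the screening questions". Under Recruitment, those meeting the eligibility criteria are invited. They are randomized once the survey and HIPAA authorization are back, and the packet follows within 7 days. At that stage, "Participants in Arm 3 also receive the dermatoscope and instructions for attaching it to their smartphone". The description of Arm 3 says the dermatoscope "permits acquisition of dermoscopic images through the participant’s smartphone camera", so teledermoscopy depends on the participant's own device.

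**The concern.** A person with a smartphone or tablet that does not take the DermLite fails criterion 6 but passes the screening rule. Nothing described between screening and randomization would catch this.

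The mismatch matters in one arm only. In Arms 1 and 2 no dermatoscope is supplied, so compatibility has no bearing on what participants receive. In Arm 3 it decides whether the added component can be used at all. The Discussion presents the trial as isolating the effect of each added component, and the Arm 3 versus Arm 2 comparison carries that purpose for teledermoscopy. Arm 3 participants who cannot use the device pull that comparison towards no difference. The same applies to the time from finding a lesion to the diagnostic visit, since Table 1 gives shorter waits for dermatology review as the barrier that teledermoscopy is meant to reduce.

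**Working it through.** **Step 1: the text.** Take a person with an incompatible smartphone who meets every other criterion.

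| Stage | Result for this person |
|---|---|
| Study participants, criterion 6 | Not eligible |
| Eligibility screening, question 4 | Answers yes |
| Eligibility screening, closing rule | Eligible |
| Recruitment | Invited if taken to meet the criteria; no compatibility check described |
| Arm 3, if assigned | Is sent a dermatoscope that may not fit |

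The first and third rows conflict.

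**Step 2: reproduce the plan's power.** Inputs from Power calculations: 2-df chi-squared test, n = 200 per arm, alpha 0.025, PAE rate 30%, at least one other arm 15 points higher, stated power 85%.

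Noncentrality = n × Σ(pᵢ − p̄)² / [p̄(1 − p̄)]. The critical value is −2 ln(0.025) = 7.378.

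- Rates 30/30/45%: p̄ = 0.35 and Σ(pᵢ − p̄)² = 0.015. Noncentrality = 200 × 0.015 / 0.2275 = 13.19, power 85.9% (85.5% in 200,000 simulated trials).
- Rates 30/45/45%: p̄ = 0.40 and Σ(pᵢ − p̄)² = 0.015. Noncentrality = 3.0 / 0.24 = 12.5, power 83.7% (84.9% simulated).

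Both agree with the stated 85% to within 2 points. The plan's power figure is not in dispute.

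**Step 3: hypothetical worst case.** The documents give no incompatibility rate, so f, the share of Arm 3 without a compatible device, is an assumption and is shown over a range. Assume also that physician activation adds nothing, that teledermoscopy supplies the full 15 points, and that the share f gets none of it. The rates are then 30/30/(45 − 15f)%. With d = 0.15(1 − f), Σ(pᵢ − p̄)² = (2/3)d².

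| f | Arm 3 rate | d | Noncentrality | Power |
|---|---|---|---|---|
| 0 | 45.0% | 0.1500 | 13.19 | 85.9% |
| 5% | 44.25% | 0.1425 | 2.7075 / 0.2267 = 11.94 | 81.7% |
| 10% | 43.5% | 0.1350 | 2.43 / 0.2260 = 10.75 | 76.8% |
| 20% | 42.0% | 0.1200 | 1.92 / 0.2244 = 8.56 | 65.2% |

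In this case power falls below the planned 80% somewhere between f = 5% and f = 10%.

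**Step 4: the opposite case.** Suppose physician activation supplies the gain, giving 30/45/45%. Arm 3 participants with incompatible devices still receive physician activation and keep the gain. The rates do not depend on f, and power stays at 83.7%.

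**The case against.** Several points can be made for the plan.

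- **Other wording may carry criterion 6.** The Recruitment section invites those who meet the eligibility criteria, and the screening questions go to people who already fulfill criteria listed earlier. If both phrases mean the full numbered list, compatibility is formally required before invitation. This reading is weak. Questions 2 and 3 would then re-ask things already established (a provider visit and a text-capable phone). The closing rule still rests on the four answers, and neither phrase describes how compatibility would be known. It does show that wrongful enrollment is possible under the printed rule, not certain.
- **The article is condensed.** The actual screening form may carry a device list. That is possible, but the article prints the questions and the decision rule, and these conflict with its own criterion. The point is a stated inconsistency, not an omitted detail. If the form does hold a list, only the text needs correcting.
- **The power loss depends on assumptions.** This stands. The share f is unknown, the worst case credits teledermoscopy with everything, and the calculation concerns physician screening, not waiting time.

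A reader might go further and infer that some Arm 3 participants cannot receive their intervention. The documents do not show this. They report no incompatible participant, and the Discussion says the device attaches readily to a range of smartphones and tablets. "In addition to PAE + MD, Arm 3 participants receive a dermatoscope", so an affected person loses only the use of teledermoscopy. A reader might also fear exclusions after randomization in Arm 3 alone. The protocol proposes none. With everyone analyzed as randomized, the consequence is dilution of the contrast.

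**Conclusion.** The inconsistency is real. The screening rule is looser than criterion 6, and the article describes no later compatibility check before randomization, so people who fail a stated criterion can be randomized. Those assigned to Arm 3 may be unable to use teledermoscopy, which would dilute the Arm 3 versus Arm 2 contrast.

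The size of the dilution cannot be determined from the documents. It runs from no loss of power on the physician-screening outcome, if physician activation supplies the gain, to the worst-case figures above, which rest on an assumed f and on teledermoscopy supplying the entire gain. The point deserves correction because it touches the one contrast that isolates teledermoscopy and is cheap to put right.

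**What to change.** Reconcile the two sections. Reword screening question 4 to ask for the make and model of the device, or for access to one of a named list of DermLite-compatible devices. Apply it before randomization, identically for all arms, and let the closing eligibility rule refer to it.

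For participants already enrolled, record device compatibility in all three arms and keep everyone in the as-randomized analysis. This makes f known and allows the dilution to be described without removing anyone.

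The cost is one reworded question and a few more screen failures. The Trial status section says recruitment was not complete at submission, so at that point the change could still have applied to those yet to be screened.

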### Recruitment

The study protocol was reviewed and approved by the Institutional Review Board of Harvard TH Chan School of Public Health (approval number: IRB12-0002). Participants who meet study eligibility criteria will be invited to enroll. The invitation packet includes the invitation letter, Health Insurance Portability and Accountability Act (HIPAA) authorization, consent form, and the baseline survey.

Upon receipt of the completed survey and HIPAA authorization, the participant is officially enrolled in the study and randomized to one of three study arms. Within 7 days of randomization, each participant receives an enrollment packet that includes: a letter welcoming them to the study; print materials about their skin cancer risk, how to conduct skin self-examinations, an appointment checklist providing tips and suggestions about physician skin examinations for participants to reference when they go to see their doctor; and details about how to access the study website. Participants in Arm 3 also receive the dermatoscope and instructions for attaching it to their smartphone, using it, and uploading photos to the photo repository.

### Intervention components

The key intervention components are summarized in Table 1. The content of developed materials was partially influenced by Key Informant Interviews (n = 6, 50% female) conducted with members of the study cohort from which participants are being recruited. Common themes from these interviews regarding skin cancer knowledge and screening practices, attitudes about survivor status, preferences for receiving health information, and Internet and mobile phone connectivity and use were foundational in designing the communication strategy that guided development of the study’s name, logo, website, and print materials. A key development in the functionality and user-friendliness of the intervention is the added development of a specially designed mobile interface of the study website for convenient and functional access on mobile devices such as mobile phones and tablets. Provider intervention materials were guided by discussions with both primary care physicians and physician specialists. The study name/logo, website, educational print materials, and image repository were developed by the Health Communication Core of Dana-Farber Cancer Institute (www.healthcommcore.org) in collaboration with study staff.

**Table 1 Tab1:** **Core intervention components of the three arms**

	**Intervention strategy**	**Content**	**Mediating variables addressed**
PAE	• 14 text messages	• 1 text: welcoming participants to the study	• PAM components:
		• 12 texts: reminders to conduct thorough skin self-examinations (TSSE), prompts to see a health care provider (HCP) for suspect lesions, messages highlighting key areas on targeting mediators and suggesting relevant website content (for example, demo of TSSE, risk factors for skin cancer)	
			Playing an active role in early detection
		• 1 text: reminding participants about the 18-month survey	Self-efficacy re TSSE and asking HCP for skin exam
	• Study website	• Information about skin cancer risk among survivors, and the key role that skin self-examinations and early detection (ED) play	
			Knowledge/awareness
			Taking action
			**•** Risk perception: re cancer status
		• Information about how to conduct a self-examination and clinical images illustrating what to look for	
		• Information about how to ask a HCP for a skin exam:	**•** Barrier reduction
		Printable checklist	
		Guide to discussion	
		• Information about preventive behaviors	
		• Interactive skin exam quizzes	
		• Tips for making ED a priority	
		• Lay summaries of research on the efficacy of skin exams	
		• Videos and links to additional resources about skin cancer	
PAE + MD (Additional components/Mediators addressed)	• Physician activation packet	• Introduction letter describing intervention and encouraging MDs to do a full-body skin examination at the patient’s next visit	**•** Self-efficacy to perform a skin examination on the patient
		• Guide to conducting a full skin cancer examination	
		• Information about survivors’ increased risk of skin cancer	
		• Access to the provider section of the ASK website, which houses additional resources including clinical images illustrating what to look for	
	• Study website	• Information about skin cancer risk among survivors, and the key roles that skin exams and early detection (ED) play	**•** Barrier reduction related to HCP provision of skin examination (for example, how to do exam; how to identify suspicious lesions)
		• Video demonstration of how to conduct a thorough clinical skin examination	
		• Summaries of research on the efficacy of skin exams	
		• Videos and links to additional resources regarding skin cancer	
		• Access to all participant website materials	
PAE + MD + TD	• Telederm	• Participant given dermatoscope attachment	**•** Barrier reduction decrease wait times for dermatology review of lesions
		• Website provides information about typical and atypical lesions	
		• As part of regular TSSE, participant takes photographs of suspect lesions and sends to study dermatologist	
		• Teledermoscopy report sent within 1 week, includes instructions to health care provider about needed follow-up or treatment	

Abbreviations: PAE, Patient Activation and Education, PAE + MD, PAE plus physician activation; PAE + MD + TD, PAE plus physician activation, plus teledermoscopy, PAM, Patient Activation Measure.

#### Arm 1: Patient Activation and Education

All participants receive educational print materials; access via individual login to the study website, which provides additional information, videos, and images of abnormal lesions; text messages designed to prompt use of the website and the target behaviors; and study staff contact information. After receipt of the introductory materials packet, participants are encouraged to use the study website for education about typical and atypical lesions, and then to examine themselves for any lesions of concern. It is anticipated that employment of the PAM will guide participants toward increased awareness of their risk of skin cancer while positively encouraging them to engage in recommended screening behaviors. Participants receive 14 separate text messages (Table 2 for examples) throughout the 18-month period designed to encourage them to: (1) carefully examine their skin for cancer with the aid of the study’s tools, such as pictorial diagrams and photographs of abnormal lesions for reference; (2) discuss concerns with and request skin exams from their physicians utilizing a checklist that they can print to bring to their physician visit or access on the mobile study site during their appointment; and, (3) develop a collaborative care plan (between the physician and participant) including common responsibility for monitoring and quickly following up on new and changing moles and lesions.

**Table 2 Tab2:** **Select text messages sent to participants over the 12-month study and follow-up period**

**Type of message**	**Message content**
Early detection Physician exam	ASK! Your past radiation treatment increases your skin cancer risk. Checking your skin monthly and asking for a Dr.’s exam are vital to catch & treat it early.
Early detectionPhysician exam	ASK! Your doctor is more likely to examine your skin if they know of your skin cancer risk. Here’s how to ask for an exam & an appt checklist: bit.ly/
Early detectionPhysician exam	ASK! If your doctor refers you to a dermatologist or other doctor for a mole or area of concern on your skin, follow-up right away! Here’s why: bit.ly/
Early detectionWebsite/Educational	The ABCDE rule will help you find unusual moles during your monthly skin self-check. More on the ABCDE rule & pictures plus watch a video: bit.ly/
Early detection Educational	ASK! Melanoma, the most serious form of skin cancer, “writes its message in the skin for all to see”. Check yourself regularly for anything unusual & follow up!
Early detectionWebsite	Thanks for being a part of ASK! Do a total skin check monthly–carefully looking at your skin from head to toe and front to back. Here’s how: bit.ly/
Early detectionWebsite/Educational	ASK! Skin cancer can grow from existing moles and damaged skin. Get to know your skin. Check for any changes. You’ll get better each time. Tips: bit.ly/

#### Arm 2: Patient Activation and Education plus physician activation

In addition to the PAE elements, participants’ physicians are mailed physician activation materials. The goal of the physician activation intervention is to increase provider knowledge about the importance of early detection for survivors, with a particular focus on this specific population, motivate these providers to educate and screen patients, and to provide them with the skills and confidence needed to perform clinical examinations. Provider intervention materials include: (1) an introduction letter describing the intervention and examination recommendations; (2) information about increased risk of skin cancer for adult survivors treated with radiation and the role of primary care in early detection and treatment; (3) instructions on how to conduct a full skin cancer examination; and, (4) access to the study website, with specific information for health care professionals that contains resources and images to assist in conducting skin exams and identifying potential skin cancers. Providers are also given access to the new web-based curriculum guide developed by the INFORMED study of skin screening for primary care physicians [46,47]. Physicians are provided with a study 1-800 number should they have questions regarding the examination or follow-up care or need help ensuring an expedited referral to a dermatologist from the American Academy of Dermatology.

#### Arm 3: Patient Activation and Education plus physician activation and teledermoscopy

In addition to PAE + MD, Arm 3 participants receive a dermatoscope that permits acquisition of dermoscopic images through the participant’s smartphone camera and instructional materials for use of this attachment including a customized instructional video. Participants can take high-resolution photographs of suspect moles or lesions and upload these photos via a secure web portal for review by the study dermatologist. Participants are instructed to ask significant others to take photographs of back-of-body lesions. A letter with the results of the assessment of submitted photographs to the study website will be sent to the participant’s identified physician encouraging the physicians to emphasize the importance of monthly self-examinations and encouraging referral to a dermatologist for a clinical examination, if necessary. Participants are informed that they must contact their physicians to receive dermoscopy reports. Participants have access to teledermoscopy for 12 months after enrollment.

The study staff, in cooperation with 3Gen, the manufacturer of the DermLite, developed written and video instructional materials to assist participants in effectively using the DermLite attachment and ensuring proper upload of photographs taken to be reviewed by the study dermatologist. The DermLite (Figure 2) is a portable dermatoscope that can be attached to smartphones and tablets and is primarily used for the examination of suspicious skin lesions. It consists of a magnification lens and light-emitting diode (LED) lighting that allows high-quality visualization of subsurface skin structures that are not typically visible to the naked eye. Advantages of this technology are that it can facilitate detection of skin cancers in the early stages of development and offers the possibility of increased convenience for both physicians and patients as it has the potential to be performed by the patient and sent remotely to a physician specialist. Print and online materials provided for Arm 3 participants include step-by-step instructions regarding the use of the DermLite, troubleshooting tips, and detailed instructions about uploading photos via the study website.

